#### Follow-up

Follow-up timepoints include immediately, 7 days, 1 month, 6 months, 1 year, 1.5 years, 2 years, 2.5 years and 3 years after surgery. Follow-up will include physical examination, enhanced CT/MRI, bilateral neck B-scan ultrasonography, Constant–Murley score and a safety observation. There will be different evaluations at different timepoints, but overall evaluation will be the same between the two groups. The number of patients who quit our trial for any reason during follow-up will be represented as *m*_3_, and the number of patients who will be included in our analysis will be represented as *n*_4_ (see Fig. 3 for details).

**Fig. 3 Fig3:**
[figure not shown]
Timeline of trial. CT computed tomography, MRI magnetic resonance imaging

### Sample size

In calculating the sample size, we assumed the 3-year OS rate in the IIb retention group will be about 78%, α = 0.05 (one-sided), power of 80% (β = 20), and that in the IIb dissection group will be 80% [1]. The noninferiority margin will be 12%, so the sample size as generated by PASS Sample Size Software 15.0 (NCSS LLC, Kaysville, Utah, USA) will be 261 for IIb retention and 260 for IIb dissection. To obtain a reasonable sample size and make sure the trial is instructive for clinical work, we combined the common opinions of oral and maxillofacial experts, and the statistician defined the noninferiority margin as 12% [24]. Although the value seems to be large, its role is to control the large sample size that would otherwise be unapproachable.

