**Methods:**

We designed a parallel-group, randomized, non-inferiority trial that is supported by Shanghai Ninth People’s Hospital, Shanghai Jiao Tong University, School of Medicine, Shanghai, China. We will enroll 522 patients with early oral carcinoma who match the inclusion criteria, and compare differences in 3-year overall survival, progression–free survival (PFS) and HRQoL under different interventions (retention or dissection of level IIb). The primary endpoints will be tested by means of two-sided log-rank tests. Analysis of overall and progression-free survival will be performed in subgroups that were defined according to stratification factors with the use of univariate Cox analysis. In addition, we will use post-hoc subgroup analyses on the basis of histological factors that were known to have effects on survival, such as death of invasion of the primary tumor. To evaluate HRQoL, we will choose the Constant–Murley scale to measure shoulder function.

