#### Intervention

The number of patients who must be removed from our trial for any reason during intervention (surgery) will be represented as *m*_2_, and the number of patients during follow-up will be represented as *n*_3_ = *n*_2_ − *m*_2_.

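### The enrolment target of 522 is in effect the uninflated calculated sample size (261 + 260 = 521), so the stated 80% power makes no allowance for loss; whether power then falls below 80% depends on which alpha applies

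*Protocol article*

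**What the plan says.** The Sample size section sizes a non-inferiority comparison of two 3-year overall survival (OS) proportions.

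- Experimental arm: "we assumed the 3-year OS rate in the IIb retention group will be about 78" per cent.
- Control arm: "that in the IIb dissection group will be 80" per cent.
- Error rates: "α = 0.05 (one-sided), power of 80% (β = 20" per cent). The margin is 12 percentage points.
- Result: "the sample size as generated by PASS Sample Size Software 15.0 (NCSS LLC, Kaysville, Utah, USA) will be 261 for IIb retention and 260 for" the dissection arm. The section mentions no allowance for loss.

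The Methods paragraph of the abstract gives the target: "We will enroll 522 patients with early oral carcinoma who match the inclusion criteria".

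The Participant timeline then takes patients out in two steps after randomisation. Under Intervention, those removed at surgery are m2, and "the number of patients during follow-up will be represented as" n3 = n2 − m2. Under Follow-up, the text continues: "The number of patients who quit our trial for any reason during follow-up will be represented as" m3, after which the analysed number is called n4. No rate is given for m2 or m3.

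Under Statistical methods, OS is to be tested with a two-sided log-rank test, with no significance level stated. Under Data collection methods, survival status is to be obtained by telephone at each timepoint.

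**The concern.** A calculation for two 3-year proportions assumes that 3-year status is known for every patient counted in it. If 521 is that number, enrolling 522 leaves one patient to cover all losses at surgery and over three years of follow-up. The plan expects losses at both stages, so the 80% is attached to a number that the plan itself does not expect to analyse in full.

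In a non-inferiority trial, lost power means a greater chance of an inconclusive result. If power at the analysed number is below 80%, readers and the ethics committee have been given too favourable a figure. Whether it is below depends on the significance level, and the article is not consistent on that.

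**Working it through.** **Inputs.** From the Sample size section: retention 0.78, dissection 0.80, margin 0.12, power 0.80, 261 and 260 patients. The distance from the assumed difference to the margin is 0.12 − 0.02 = 0.10. The documents give no loss rate, so losses of 5% to 20%, equal in both arms, are my assumption.

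**Step 1: reproduce the printed size.** Unpooled normal approximation, per arm:

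n = (0.78×0.22 + 0.80×0.20) × (z_α + z_0.80)² / 0.10² = 0.3316 × (z_α + 0.8416)² / 0.01

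- One-sided 0.05, as printed: (1.6449 + 0.8416)² = 6.183, n = 205.01, so 206 per arm and 412 in total. This does not match. Pooled (205.1), restricted-likelihood score (206.8) and continuity-corrected (224.6) versions do not match either.
- One-sided 0.025: (1.9600 + 0.8416)² = 7.849, n = 260.27, so 261 per arm and 522 in total. This matches, with no term for loss.

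The uneven pair fits as well. With SE = √(0.1716/n1 + 0.16/n2) and power = Φ(0.10/SE − z_α), at one-sided 0.025:

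- 260/260: SE = 0.03571, power 79.96%.
- 261/260: SE = 0.03568, power 80.04%.

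**Step 2: power if lost patients are dropped.** Same formula, with n1 = 261(1 − L) and n2 = 260(1 − L).

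| Assumed loss L | Analysed | Power, one-sided 0.025 | Power, one-sided 0.05 |
|---|---|---|---|
| 0% | 521 | 80.0% | 87.7% |
| 5% | 495 | 78.0% | 86.2% |
| 10% | 469 | 75.8% | 84.5% |
| 15% | 443 | 73.4% | 82.6% |
| 20% | 417 | 70.8% | 80.6% |

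At one-sided 0.025 the cost passes 5 points at about 12% loss. At one-sided 0.05 the 80% holds until about 1 − 412/521 = 21% loss.

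**Step 3: power if everyone is kept and leavers are censored.** The Kaplan-Meier difference at 3 years is used with Greenwood variance, assuming exponential survival and an exponential loss hazard. With H = −ln S and C = −ln(1 − L), the variance per arm is S² × H/(H + C) × (1/[S(1 − L)] − 1) / n.

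For L = 10%:

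- Retention: 0.6084 × 0.7023 × 0.4245 / 261 = 0.000695.
- Dissection: 0.6400 × 0.6793 × 0.3889 / 260 = 0.000650.
- SE = √0.001345 = 0.03668, and 0.10/SE = 2.726.
- Power at one-sided 0.025: Φ(2.726 − 1.960) = 77.8%, against 75.8% with dropping.
- Power at one-sided 0.05: Φ(2.726 − 1.645) = 86.0%, against 84.5%.

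For L = 20% at one-sided 0.025, the same formula gives about 75%, against 70.8% with dropping.

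**The case against.** A reader might infer that the trial is underpowered. On the printed inputs that does not follow. The protocol prints a one-sided alpha of 0.05; at that level about 412 patients are needed, and 521 keeps at least 80% power up to about 21% loss. The shortfall appears only if the printed alpha is replaced by 0.025. That value is inferred from the match with 261/260 and from its fit with a conventional two-sided 0.05 test. This objection stands, and it is why the point is conditional.

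A hidden reserve also cannot be strictly excluded: 206/(1 − 0.20) rounds up to 258 per arm, 516 in total, close to 521. It is the weaker explanation, because it misses 261/260 while one-sided 0.025 reproduces that pair, and because the text mentions no reserve.

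A reader might also infer that everyone who quits is deleted from the survival analysis. The visible text does not say so. Removal at surgery is explicit (n3 = n2 − m2), but the formula for n4 is not in the text, and the section refers to a figure that is not shown here. A log-rank analysis can censor leavers.

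Finally, the primary outcome is vital status collected by telephone, with a further telephone inquiry after a missed visit, so loss for OS may be small. At one-sided 0.025, 2% loss with dropping still gives 79.2%.

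None of this supplies what is missing between the printed figures: the article states an N, a power and a patient flow, and does not say which N the power refers to.

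**Conclusion.** The point holds in conditional form. The enrolment target is in effect the uninflated calculated size, although the plan's own flow loses patients before analysis. Under either alpha, the stated 80% is not in general the power at the analysed number.

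- At one-sided 0.025, any loss takes power below 80%. At the assumed 10% loss the cost is about 4 points if patients are dropped and about 2 if they are censored; at 20% it is about 9 and 5.
- At the printed one-sided 0.05, no shortfall is shown up to about 21% loss, and the 80% understates the power.

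The alpha therefore has to be settled first. The loss figures rest on assumed rates equal in both arms; the censored figures also assume exponential survival and loss. The mismatch between target, calculation and flow needs no such assumption.

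**What to change.** 1. **Sample size section.** State the alpha that will be used for the non-inferiority conclusion and make it agree with the planned test. Say that 261 and 260 are randomised patients, give an expected loss to 3 years, and restate the power at that loss. With 10% loss as an example, the statement would be about 76% (dropped) or 78% (censored) at one-sided 0.025, or about 84% or 86% at one-sided 0.05.
2. **Participant timeline (Intervention, Follow-up) and Data collection methods (Primary outcome).** Keep all randomised patients in the OS analysis, based on the Kaplan-Meier difference at 3 years. Keep following patients counted in m2 for survival. Censor those who leave at the last date they were known to be alive, taken from the telephone contacts already planned. Report m2 and m3 as flow counts and do not subtract them from the analysis.

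The cost is wording in these paragraphs, with no extra patients or procedures. If one-sided 0.025 is confirmed, the stated power becomes slightly less favourable. The Trial status section says that enrolment had not started, so the change could be made before any patient was affected.

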### Statistical methods

#### Overall survival

This trial will be terminated when the last patient has been followed-up for 3 years. After the trial ends, the primary endpoints will be tested by means of two-sided log-rank tests.

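### The sample-size inputs as stated, including one-sided alpha 0.05, give about 206 per arm rather than 261/260; the printed figure matches one-sided 0.025, so the alpha used needs confirming

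*Protocol article*

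**What the plan says.** All the planning inputs are in the Sample size section of the protocol article. The error rates are given as "α = 0.05 (one-sided), power of 80" per cent. Assumed 3-year overall survival is 78% in the retention arm and 80% in the dissection arm, and the non-inferiority margin is 12%. The section attributes the result to PASS 15.0 and says that it "will be 261 for IIb retention and 260 for IIb dissection". It mentions no allowance for loss to follow-up.

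Two other places bear on this. The abstract gives the total: "We will enroll 522 patients with early oral carcinoma". Under Statistical methods, Overall survival, the article says that "the primary endpoints will be tested by means of two-sided log-rank tests". Neither the abstract nor that section attaches a significance level to the word two-sided.

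**The concern.** Sample size for a non-inferiority comparison of two proportions is fixed by the two rates, the margin, alpha and power. The section states all five and then a result that does not follow from them. The gap is 261 against 206, about 27%, which is too large to be rounding or a choice of variance formula.

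At stake is the error level of the primary conclusion. One-sided 0.05 corresponds to the bound of a 90% confidence interval, and one-sided 0.025 to the bound of a 95% interval. The text states the first; the arithmetic points to the second. In a non-inferiority trial with survival as its primary outcome, the level should be unambiguous before data exist, and the power claim should belong to that level.

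**Working it through.** **Inputs** (all from the Sample size section): p_R = 0.78 (retention), p_D = 0.80 (dissection), margin M = 0.12, one-sided alpha 0.05, power 0.80. The margin is read as an absolute difference in 3-year survival. The section does not say so, but this reading is the one that reproduces the printed figure below.

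**Formula** (unpooled normal approximation, equal arms):

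n per arm = (z_α + z_β)² × [p_R(1 − p_R) + p_D(1 − p_D)] / [M − (p_D − p_R)]²

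Variance term: 0.78 × 0.22 + 0.80 × 0.20 = 0.1716 + 0.1600 = 0.3316. Denominator: (0.12 − 0.02)² = 0.01.

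**Attempt to reproduce 261/260 with alpha as stated**

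(1.645 + 0.842)² × 0.3316 / 0.01 = 205.0, so 206 per arm.

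**Does the method explain the gap?**

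| Method, 80% power | One-sided 0.05 | One-sided 0.025 |
|---|---|---|
| Unpooled | 205.0 → 206 | 260.3 → 261 |
| Pooled | 205.1 → 206 | 260.4 → 261 |
| Farrington-Manning | 206.8 → 207 | 262.7 → 263 |
| Continuity-corrected | 224.6 → 225 | 279.9 → 280 |

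Nothing in the 0.05 column is near 261. Changing only alpha to one-sided 0.025 gives (1.960 + 0.842)² × 0.3316 / 0.01 = 260.27. Twice that is 520.5, which rounds up to 521 and splits as 261 and 260, as printed.

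**Power at 261/260**

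SE = √(0.1716/261 + 0.1600/260) = 0.0357, and 0.10/SE = 2.803.

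- One-sided 0.05: Φ(2.803 − 1.645) = 87.7%.
- One-sided 0.025: Φ(2.803 − 1.960) = 80.0%.

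**Other routes to 261**

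- Higher power at one-sided 0.05: 239 per arm at 85% and 284 at 90%. No match.
- Log-rank non-inferiority: margin hazard ratio ln 0.68 / ln 0.80 = 1.73, assumed hazard ratio ln 0.78 / ln 0.80 = 1.11. At one-sided 0.05, events = 4 × (1.645 + 0.842)² / (ln 1.73 − ln 1.11)² ≈ 128 (unrounded ratios). With 3 years of follow-up each, 128/0.21 ≈ 609 in total, about 305 per arm; at 0.025, about 387 per arm. No match.
- Loss allowance at one-sided 0.05: 206/0.79 = 260.8, so 261. A loss of about 21% fits, but none is stated.

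**Effect of losses.** The article gives no loss rate, so 10% and 15% are assumptions:

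| Analysed per arm | Power, one-sided 0.025 | Power, one-sided 0.05 |
|---|---|---|
| 261/260 (no loss) | 80.0% | 87.7% |
| 235 (10% lost) | 75.9% | 84.5% |
| 222 (15% lost) | 73.5% | 82.7% |

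**Total.** 261 + 260 = 521; the abstract says 522, which is 2 × 261.

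**The case against.** The strongest reply is that nothing here harms the trial as written. At the stated alpha, enrolment is larger than needed and 80% power survives a loss of about 21%. That is correct, and it is why this is not a finding of inadequate power.

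A second reply is that 0.025 is reverse-engineered. The software output is not shown, and a loss allowance could produce the same number. A log-rank calculation at one-sided 0.05 with staggered entry and a 3-year minimum follow-up could also come close: about 532 in total with 1 year of accrual and 502 with 1.5 years. This also stands, in that 0.025 is likeliest rather than established. The alternatives need a loss rate or an accrual period that the article does not give, whereas the change of alpha alone matches exactly. On any of these explanations, the section's stated inputs still do not yield its stated output.

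A reader might infer that the protocol sets two conflicting levels, so that the false non-inferiority rate is 2.5% or 5% depending on the section followed. The text does not support this. The only level written anywhere is one-sided 0.05, and the two-sided log-rank wording carries no alpha. As worded, that test also addresses a difference rather than non-inferiority, which is a separate matter. A statistical analysis plan that is not shown may fix the confidence level.

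A reader might also infer that the change of level moves the largest passing survival deficit from 5.0 points (12 − 1.96 × 3.57) to 6.1 points (12 − 1.645 × 3.57). Those figures assume a Wald comparison of 3-year proportions, which the article does not specify. They show scale only.

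**Conclusion.** The sample-size statement is wrong as written. Its inputs need about 206 per arm, not 261/260, and 261/260 has 87.7% power at the stated alpha. One-sided 0.025 reproduces the printed figure exactly and is the likeliest source. The article does not show whether the slip lies in the value 0.05 or in the word one-sided (two-sided 0.05 also gives 261), nor does it exclude an unstated loss allowance.

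The conclusion rests on an absolute 12-point margin and a comparison of 3-year proportions. If 0.025 was used, the 80% power leaves no room for losses; if 0.05 is intended, there is ample room. The 521 against 522 discrepancy is one patient, consistent with rounding up to equal arms, and has no practical effect on power. Severity: should-fix.

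**What to change.** Confirm from the PASS record which alpha was entered, and correct the Sample size section before enrolment; the Trial status section says that enrolment has not started.

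- If it was 0.025: state one-sided 0.025 (the bound of a two-sided 95% confidence interval), and say that 80% power assumes complete 3-year vital status, falling to about 76% if 10% are lost (an assumed rate).
- If one-sided 0.05 is really intended: restate the power as about 88%, or state the loss allowance that takes 206 to 261.

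In either case, name the same level for the primary non-inferiority confidence limit, since the abstract and the Overall survival analysis section say only two-sided. Give one total, 521 or 522, in both places.

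The cost is a sentence or two of text. Enrolment and procedures do not change.

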### Assignment of interventions

A statistician will write randomized code to generate a repeatable randomized number table. To reduce the predictability during enrollment, the statistician will determine block length, and a team that is not involved in our trial will keep all the blind codes safely. This team will create opaque sealed envelopes according to the randomized number table, and we will distribute patients according to this table.

### Stratification

OS can be affected by many factors, such as T stage (T1, T2), primary subsite (tongue, buccal mucosa, mouth floor, gingiva, posterior molar region or hard palate), and depth of invasion [25]. To balance the number of patients between groups and minimize the bias of the trial, we will use T stage and primary subsite for stratification.

### Blinding

Since the intervention in this clinical trial is a surgical procedure and the surgical records can be queried, surgeons and patients know the specific grouping information. After the trial we will send the data to statisticians and the evaluator who will be blinded to the groups.

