#### Secondary outcomes

The secondary outcomes are HRQoL and progression-free survival (PFS). For HRQoL, we will use the Constant–Murley scale to evaluate patients’ shoulder function, with follow-up at 7 days, 21 days, 3 months, 6 months, 1 year, 2 years and 3 years after surgery.

There are many reasons for setting OS as the primary outcome. First, it is widely used as a reliable indicator for evaluating the prognosis of tumors. It is reported that the 3-year OS rate in an IIb dissection group is about 80% [1], which includes disease-free survival and living with disease. Metastasis in level IIb is extremely low, and even if it happens it is nonlethal and can be instantaneously controlled by surgery or radiotherapy. Theoretically, 3-year OS in the IIb retention group will resemble that in the dissection group. A summary of 38 RCTs [7, 23] reports no significant association between PFS duration and HRQoL. In addition, as PFS is not as reliable as OS and can also increase difficulties in follow-up, we did not use PFS as the primary outcome.

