#### Secondary outcomes

For HRQoL, we will use the Constant–Murley scale to evaluate shoulder function at each follow-up timepoint. In order to improve the reliability of shoulder function evaluation, two clinicians will be systematically trained on use of the scale.

For PFS, observations will start at time of randomization and end when events (see below) occurred. In the period of time from randomization (Fig. 3) to any primary recurrence, local metastasis, distant metastasis, and other life-threatening events or death will be defined as PFS.

If a patient has not returned to the clinic for more than 2 months after the follow-up timepoint, a telephone inquiry will be conducted.

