### Data management

All paper versions of the original materials will be photographed and saved in an encrypted database. All electronic data will be stored in the electronic medical records of the Shanghai Ninth People’s Hospital. All procedures for evaluating shoulder function will be filmed and saved.

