#### HRQoL

We will use a repeated analysis of variance (ANOVA) measure to analyze changes in Constant–Murley score between the two groups. It is reported that about 67% of patients have shoulder syndrome after neck dissection even if the accessory nerve is spared [26]. Currently, two methods might work to deal with the problem of shoulder dysfunction. The first is to restore the damaged nerve with such methods as intraoperative brief electrical stimulation of the spinal accessory nerve (BEST SPIN). However, this technique has little effect [27], and literature on the treatment of damaged accessory nerves is rare. The second is retention of level IIb during surgery to preserve the integrity of accessory nerve function and structure. By measuring changes in the action potential of the accessory nerve during surgery it was found that level IIb dissection can greatly damage the accessory nerve [6]. We will use the Constant–Murley scale [28] to assess shoulder function. Although the scale’s reliability in evaluating shoulder function has been questioned [29], it has been clinically applied for more than 30 years, and it can reflect both subjective indicators (such as pain or daily activity) and objective standards (such as the muscle mobility and power). Because of the tissue defect caused by primary resection, distant free or adjacent flaps are used to restore it. In order to ensure the flaps are alive, movement control after surgery is crucial. Patients with free flaps are clinically permitted to lift the upper body on the fifth day after surgery and can also sit up in bed. On the sixth day after surgery, mild activities such as walking are permitted. Therefore, the first timepoint for evaluating shoulder function will be the seventh day after surgery, and then there will be follow-up at 1 month, 6 months, 1 year, 2 years and 3 years.

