## Discussion

For decades, the treatment of early-stage oral cancer has created an apparent dilemma between survival and HRQoL [1, 30–33]. To guarantee a higher survival rate, HRQoL must often be sacrificed. The neck metastatic rate in early-stage OSCC is about 30% [34], and methods of neck treatment include therapeutic dissection and observation. Data from India [1] showed that the 5-year survival rate is about 13% higher in the therapeutic group than in the control group, but overtreatment still happens in those patients whose neck lymph nodes are actually negative. As far as we know, this is also true for the treatment of breast cancer. Axillary lymph node metastasis often appears in early-stage breast cancer, at a rate of about 15–20% [35]. Previously, axillary dissection was the gold standard for treating early-stage breast cancer as it reduced recurrence and improved OS, but it also brought complications such as lymphedema, which greatly affected HRQoL for patients after surgery. Sentinel-lymph node biopsy has since replaced axillary dissection as it offers better disease control and HRQoL [36–38]. There are therefore commonalities between breast and oral cancer in their early stages.

Because there is higher occult metastasis in early-stage oral carcinoma than in early-stage breast cancer, and despite postsurgical HRQoL considerations, surgeons prefer to perform therapeutic neck dissection to enhance OS. During neck dissection in oral cancer, traction of the accessory nerve can decrease shoulder function, and damage to the nerve occurs when level IIb is dissected [26]. The occult metastatic rate for IIb is < 6% [5, 12–17], so if level IIb is retained the nerve will not be pulled and HRQoL for patients with early-stage oral cancer can be greatly increased. This trial is designed to assess whether IIb neck dissection should be performed in T1–T2 N0 OSCC, and to discuss its effects on survival rates and HRQoL.

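### The plan describes blinding only for people who receive data after the trial; it does not say that the two clinicians scoring shoulder function at visits are unaware of allocation or outside the surgical team

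*Protocol article*

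**What the plan says.** **Who knows the arm.** In the Blinding section of the protocol article, "surgeons and patients know the specific grouping information", because the intervention is surgical and the operative records can be looked up.

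**Who is blinded, and when.** The same section continues: "After the trial we will send the data to statisticians and the evaluator who will be blinded to the groups". It describes no other blinding step, and the evaluator's task is not defined anywhere in the article.

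**Who scores the shoulder, and when.** Under Data collection methods, Secondary outcomes, "we will use the Constant–Murley scale to evaluate shoulder function at each follow-up timepoint", and "two clinicians will be systematically trained on use of the scale". The two visit lists (Outcomes, and Statistical methods under HRQoL) differ in some timepoints, but both start at day 7 and end at 3 years.

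**What the scale contains.** Under Statistical methods, HRQoL: "it can reflect both subjective indicators (such as pain or daily activity) and objective standards (such as the muscle mobility and power".

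**Recording.** Under Data management: "All procedures for evaluating shoulder function will be filmed and saved". Nothing is said about who views the films or for what purpose.

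**Status and role of the outcome.** "The secondary outcomes are HRQoL and progression-free survival (PFS"; 3-year overall survival is primary. The Discussion gives the reason for the trial: "if level IIb is retained the nerve will not be pulled and HRQoL for patients with early-stage oral cancer can be greatly increased".

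**The concern.** A measurement is protected by blinding the person who makes it, at the time it is made. Here the blinding that is described comes into play when data are sent on after the trial, and by then each visit score has existed for up to several years. Withholding the arm from someone who receives finished scores protects the analysis but not the scoring.

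The gap falls on an outcome with a clear expected direction. The article argues that retaining level IIb spares the accessory nerve and improves shoulder function, and a rater who shares that expectation and knows the arm may score mobility and power accordingly. Training two raters improves their agreement, but it does not remove an expectation that both hold.

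Constant–Murley is the only instrument named for quality of life. It is therefore the evidence that would be set beside a survival comparison with a 12% noninferiority margin. If it is biased towards retention, readers would weigh a survival difference against a benefit that is partly or wholly an artefact of scoring.

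**Working it through.** **Step 1. Reading the sections together.**

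| Question | What the article gives |
|---|---|
| Who knows the arm? | Surgeons and patients (Blinding) |
| Who is blinded? | Statisticians and an undefined evaluator, sent data after the trial (Blinding) |
| Who is trained to score Constant–Murley? | Two clinicians (Data collection methods) |
| When is it scored? | At each follow-up timepoint, day 7 to 3 years |
| Are these clinicians kept unaware of the arm? | Not stated |
| Are they outside the operating team? | Not stated |
| Are the films scored blind? | Not stated; they are filmed and saved (Data management) |

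Blinded scoring at the visit is therefore not provided for in the text. Blinded scoring from film is possible but not stated.

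**Step 2. Which items are exposed.** Pain and daily activity are reported by patients who know their arm, and blinding a rater cannot change that. Mobility and power are measured by the examiner, and these are the items that rater blinding can protect.

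**Step 3. How large a bias would matter (illustration).** The plan states no figure on this point, so there is none to reproduce.

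Inputs:
- n = 261 per arm. The Sample size section gives 261 and 260; the abstract's 522 is 2 × 261.
- SD of the score: assumed 10, 15 or 20 points.
- Systematic scoring difference b: assumed 3 points, with no true effect.
- One timepoint, two-sided 5% test, normal approximation.

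Formulas: SE = SD × √(2/n), and P(p<0.05) = P(|Z + b/SE| > 1.96).

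With √(2/261) = 0.0875:

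| SD | SE | b/SE for b = 3 | P(p<0.05), b = 3 | P(p<0.05), b = 1.5 |
|---|---|---|---|---|
| 10 | 0.875 | 3.43 | 0.93 | 0.40 |
| 15 | 1.31 | 2.28 | 0.63 | 0.21 |
| 20 | 1.75 | 1.71 | 0.40 | 0.14 |

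The last column halves the bias, because its size is as much an assumption as the SD. The nominal rate is 0.05 throughout.

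On the SD scale with 260 per arm, a bias of 0.1, 0.2, 0.25 or 0.3 SD gives about 21%, 63%, 81% or 93%. This agrees with the table, where 3 points is 0.3 SD at SD 10 and 0.2 SD at SD 15.

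**Step 4. Allowing for deaths at 3 years.** The plan assumes 78% and 80% survival, so about 0.78 × 261 = 204 and 0.80 × 260 = 208 patients could be scored at the last visit. Then SE = SD × √(1/204 + 1/208) = SD × 0.0985, and a 3-point bias gives 0.86, 0.53 and 0.33 for SD 10, 15 and 20. The picture is similar.

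**The case against.** **The evaluator may already be a blinded film rater.** The Blinding section names an evaluator separately from the statisticians, the article uses the word evaluate for Constant–Murley scoring, and all assessments are filmed. A reader could fairly infer that the evaluator scores the films after the trial without knowing the arm. This stands as a possibility. The text does not say it, and filming would not obviously capture strength.

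**The article nowhere says the two clinicians are unblinded.** A tempting stronger reading is that the raters know the arm, or are the operating surgeons. The documents do not support it: only surgeons and patients are named as knowing, and the raters' status is left open. The supportable statement is that blinding of the visit raters is not provided for.

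**A condensed article may leave rater details to the full protocol.** This has some force, since a fuller protocol is not at hand. But the article has a dedicated Blinding section that sets out who is covered and when. Someone following it as written would not blind the visit raters.

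**Patients cannot be blinded to what they report.** The article is open about this. It limits the remedy for pain and daily activity to clear reporting, but it is no reason to leave the examiner-rated items exposed.

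**The outcome is secondary and the figures are illustrative.** Both points stand. The trial is sized on overall survival, and no formal rule trades shoulder benefit against survival. The 3-point bias has no source in the documents, and the planned analysis is a repeated-measures ANOVA rather than a single-timepoint test.

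**Conclusion.** The point holds in a limited form. The only blinding described applies to people sent data after the trial, and nothing in the article keeps the two visit raters unaware of allocation or separate from the surgical team. The mobility and power items could therefore be biased in favour of retention.

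Under assumed values (3-point bias, SD 10 to 20, 261 per arm, one timepoint, no true effect), bias alone would reach p<0.05 in about 93% to 40% of trials. Halving the bias lowers this to about 40% to 14%. These figures show that a sample sized for survival can turn a modest scoring difference into a significant one. They do not predict that it will happen: a reader might infer that any small bias would show as a significant benefit, but at SD 20 the 3-point bias is not significant in about 60% of trials.

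Nor do the documents support reading this as a threat to the primary conclusion. Survival status is little exposed to assessor expectation. The weakness concerns the secondary outcome that supplies the argument for retention, and it should be corrected on that ground.

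**What to change.** 1. **Blinding, and Data collection methods (Secondary outcomes).** State that the two trained raters are non-operating clinicians who score without access to the allocation or the operative record. Have patients asked before each assessment not to disclose their arm.
2. **Blinding.** Define the evaluator. If that role is to rate the saved films, state that this is done blind to arm and serves as a check on the mobility items.
3. **Statistical methods (HRQoL).** Report the patient-reported pain and daily-activity items separately from the examiner-rated items, labelled as unblinded.

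The cost is small. The raters, the evaluator and the films are already planned, and the Trial status section says enrolment had not started. The drawbacks are a scheduling constraint on who may rate which patient, viewing time if films are rated, and the likelihood that strength cannot be read from film. For the power items, protection therefore depends on the rater being unaware of the arm at the visit.
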